### Statistical Significance

Earlier studies have demonstrated that the volumes of the right and left hemispheric caudate nuclei are associated with one another [11]. To preserve a family-wise error rate of 5% for the two co-primary outcomes of associations between the right and left caudate nuclei and the area of secondary hyperalgesia, we will adjust for multiple comparisons of the co-primary outcomes. The two *P*-values will be evaluated at a significance level between 2.5% and 5% according to the single step method. For this method the significance level is determined by the correlation between the two resulting test statistics. If they are perfectly correlated the result will be 0.05, whereas if they are independent it will be 0.025.

*P*-values in the secondary and exploratory outcomes are evaluated at a 5% significance level, and to adjust for multiple comparisons, *P*-values are adjusted by means of single-step correction [49]. In the analysis of rs-fMRI data, the software’s standard methods and False-Discovery-Rate will be applied for correction for multiple comparisons.

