### Outcomes

#### Primary Outcome

We aim to investigate the association between the volume of the left and right caudate nuclei and the size of the area of secondary hyperalgesia induced by brief thermal sensitization. The association will be expressed in adjusted and non-adjusted R^2^and prediction intervals for the area of secondary hyperalgesia, given fixed values of the caudate nucleus’ volume.

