### Hypothesis

The area of secondary hyperalgesia and the volume of the caudate nuclei are associated, with an inverse correlation (ie, a large area of secondary hyperalgesia is associated with a small volume of the caudate nuclei).

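### Single-step adjustment of the two caudate tests is valid, but its step-down form keeps the same 5% family-wise error and would show both sides somewhat more often at no cost in participants

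*Protocol article*

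**What the plan says.** The Statistical Significance section names the left and right caudate associations as the two co-primary outcomes and sets the error target: "To preserve a family-wise error rate of 5% for the two co-primary outcomes". The two P-values "will be evaluated at a significance level between 2.5% and 5% according to the single step method", where "the significance level is determined by the correlation between the two resulting test statistics". Both P-values are therefore held to one common level, whatever happens to the other.

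The same section states that secondary and exploratory P-values "are adjusted by means of single-step correction". It makes one exception: "In the analysis of rs-fMRI data, the software’s standard methods and False-Discovery-Rate will be applied for correction for multiple comparisons".

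Three other sections matter here:

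- **Hypothesis** covers both nuclei and gives a direction: "The area of secondary hyperalgesia and the volume of the caudate nuclei are associated, with an inverse correlation".
- **Sample Size Estimation** uses the single-step level, a true correlation of -0.4 and power 0.80, and arrives at 52 participants.
- **Primary Outcome** and **Statistical Analysis of Primary Outcome** report R² and "prediction intervals for the area of secondary hyperalgesia, given fixed values of the" caudate volume. Neither mentions simultaneous confidence intervals.

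**The concern.** Under single-step, once one caudate nucleus has been declared associated, the other must still pass the stricter adjusted level. Protection against two false rejections is no longer needed at that stage, because only one hypothesis is left to test. A step-down rule uses the same correlation between the statistics and the same first hurdle, then relaxes the second test to 5%.

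What is at stake is how the result reads side by side. The hypothesis concerns both nuclei and each is tested separately. If both associations are real, a stricter second hurdle makes it more likely that only one side is declared and that the result is read as lateralised. The usual reason to accept this is that single-step yields matching simultaneous confidence intervals, and the article does not plan any.

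**Working it through.** **Inputs.** From the article: family-wise error 5%, r=-0.4, N=52, power 0.80, and a Z-test on the Fisher-transformed correlation. Assumed: two-sided tests (sidedness is not stated), the normal approximation without the age adjustment, and r=-0.4 on each side. The correlation ρ between the two test statistics is not given, so a range is shown.

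**1. Reproduce the plan's sample size.** N = ((z(1-α/2) + z(0.80)) / atanh(0.4))² + 3, with atanh(0.4) = 0.4236 and z(0.80) = 0.8416.

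- α = 0.05: ((1.960 + 0.842)/0.4236)² + 3 = 46.7, so 47.
- α = 0.025: ((2.241 + 0.842)/0.4236)² + 3 = 55.96, so 56.

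The stated 52 lies between these. At N=52 the mean of the statistic is 0.4236 × √49 = 2.966. Power 0.80 then needs a critical value of 2.966 - 0.842 = 2.124, which is a per-test level of 0.0337. That level corresponds to ρ of about 0.87. If 52 was rounded up from just above 51, the level could be as high as 0.0363, with ρ about 0.92. One-sided levels of 0.05 and 0.025 would need only 38 and 47 participants, so the two-sided reading fits. The plan's figure is reproduced.

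**2. Does step-down hold the error rate?** Let c be the single-step critical value, so that P(max|T| > c) = 5% when both nulls are true. Step-down rejects nothing unless max|T| > c, so its error under the full null is the same 5%. If only one null is true, rejecting it falsely needs its own |T| to exceed at least 1.960, which has probability 5% at most. Simulation (1,000,000 draws) gave 0.050 under the full null. With one true effect it gave 0.041 to 0.047 over ρ from 0 to 0.99. Everything that passes c under single-step also passes under step-down, so step-down never rejects less.

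**3. Size of the gain at N=52, r=-0.4 on both sides (single-step → step-down).**

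| ρ | At least one side | A given side | Both sides | Gain, both |
|---|---|---|---|---|
| 0.50 | 0.897 → 0.897 | 0.775 → 0.819 | 0.653 → 0.741 | 8.8 points |
| 0.70 | 0.876 → 0.876 | 0.785 → 0.820 | 0.694 → 0.763 | 7.0 points |
| 0.85 | 0.860 → 0.860 | 0.798 → 0.823 | 0.737 → 0.786 | 4.9 points |
| 0.90 | 0.855 → 0.855 | 0.805 → 0.825 | 0.756 → 0.796 | 4.0 points |
| 0.95 | 0.849 → 0.849 | 0.816 → 0.829 | 0.782 → 0.809 | 2.8 points |

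At ρ = 0.87, power for a given side goes from 0.800 to 0.823 and for both sides from 0.743 to 0.788. At the extremes, the both-sides gain is 11.6 points at ρ = 0 and 1.2 points at ρ = 0.99.

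The chance of declaring exactly one side when both are real is the first column minus the third. At ρ = 0.85 it falls from 0.860 - 0.737 = 0.123 to 0.860 - 0.786 = 0.074.

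**4. Unequal effects.** If one side has r=-0.4 and the other r=-0.3, at ρ = 0.87, power for the weaker side rises from 0.517 to 0.578. If only one side is truly associated, its power rises by 0.2 points or less.

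**5. Secondary regions (illustration only).** Secondary Outcomes lists eight regions. The number of tests, their correlation and their true effects are not given. In assumed families of 8 or 16 tests, with inter-test correlation 0 or 0.5 and r=0.4 wherever an effect exists, average power rises by:

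- 0 to 0.1 points with one true effect;
- about 3 to 4 points with half true;
- about 10 to 13 points with all true.

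The chance of at least one finding does not change.

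**The case against.** The strongest reply is that nothing here is wrong. The article sets a 5% family-wise error, names a prespecified method that achieves it, and sizes the study on that method; 52 participants meet the 0.80 target under the plan's own rule. This stands. The point concerns efficiency, not error control, and it shows no contradiction.

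It is also fair that the gain is small where the plan is most likely to operate. The article itself says that the two volumes are associated, and the gain shrinks as the test statistics become more correlated. No section sets a power target for showing both sides or makes success depend on both. This stands too, and limits how much weight the point can carry.

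A third reply is that the article is condensed and simultaneous intervals for the slopes may be planned elsewhere. If so, that would be a real reason to keep single-step. The outcome and analysis sections list only R² and prediction intervals, and a prediction interval for an individual area does not depend on the multiplicity method.

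Some stronger readings are not supported. A reader might infer that every secondary and exploratory P-value is affected, but resting-state fMRI has its own correction. A reader might infer that the study is underpowered, but the chance of finding at least one nucleus is identical under both rules. A reader might expect gains of 10 points or more in the secondary regions, but that needs a real association of r=0.4 in every region, and the article assumes that value only for the caudate nuclei.

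**Conclusion.** The point holds as an inexpensive improvement. Single-step is valid and consistent with N=52, but step-down holds the same 5% family-wise error, uses the same inputs and never rejects less. Nothing in the article needs what single-step offers in return. If both associations are real at r=-0.4, the chance of declaring both nuclei rises by about 4 to 5 points near ρ = 0.87, with a range of about 9 points at ρ = 0.5 to 3 points at 0.95. A given side gains about 2 points at ρ = 0.87. If only one side is real, the change is negligible. These sizes rest on two-sided tests, the normal approximation and a correlation inferred from the sample size; the direction of the comparison does not depend on them.

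**What to change.** In Statistical Significance, before the areas of secondary hyperalgesia are unblinded, state that the smaller co-primary P-value is evaluated at the single-step level and, if it is rejected, the other is evaluated at 5%. If the smaller is not rejected, neither is. Use the step-down version of the same adjustment for the secondary and the non-rs-fMRI exploratory P-values, within whatever families the plan already intends. Leave the resting-state fMRI correction as it is. The sample-size statement can also stay, because the first test keeps its level.

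The cost is a sentence of wording and a different adjustment option in R, with no added participants. Matching simultaneous confidence intervals would no longer be readily available; if the sponsor does want them, that is a sound reason to keep single-step, and the plan should say so. The timing matters, because a switch made after one side has proved significant would look data-driven.

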### Software

All statistical analyses not computed by the standard MRI software will be generated using the open source statistical programming environment R (R Foundation for Statistical Computing, Vienna, Austria).

## Discussion

We plan to investigate the association between experimental pain testing parameters and the volume, connectivity, and resting state activity of pain-relevant structures in the brain. We have designed this study to investigate basic pain physiology in healthy pain-free individuals, and we aim to investigate if any basic characteristics in the pain-free individual predict experimental pain responses. Current knowledge of basic pain physiology in humans is still sparse, and in order to compensate for the many factors that can affect pain responses, we have chosen to include a very homogenous population, consisting of healthy male volunteers between the ages of 18 and 35. The strict inclusion criteria diminish the influence of factors related to differences in the brain’s structure and function (eg, sex, age). Thus, this study aims to investigate aspects of basic pain physiology in healthy male individuals, and relevant caution should be taken when applying the results in a more heterogeneous population.

Our hypothesis, as well as our sample size estimation, are based upon previous results from Asghar et al [11]. Moreover, we wish to investigate if the volume of the caudate nuclei is associated with the size of the secondary hyperalgesia areas, indicating that this structure may be involved in the processes of central sensitization. Decreased volumes of the caudate nuclei have been demonstrated in a wide array of chronic pain patients, suggesting that these patients have a decreased ability to suppress and modulate pain stimuli [15,16,20-23,25]. With this study we plan to investigate if healthy participants with low volumes of caudate nuclei have a higher degree of central sensitization, and thus may be at a higher risk of developing chronic pain conditions.

The results of this study may also be informative for future studies and trials in the clinical setting, where pain remains a serious problem for postoperative patients. Knowledge of predictive factors and baseline pain dispositions in patients awaiting surgery may improve the design of trials on postoperative pain interventions, and improve our knowledge of the mechanisms responsible for the development of acute and chronic pain.

### Ethics

MRI uses a strong magnetic field and, unlike other imaging modalities, does not use radiation. MRI is non-invasive and has no known side effects. Due to the strong magnetic field, persons in the MRI room are not allowed to wear any metallic objects, and study participants will be informed of this prior to the MRI scans. Special MRI-compatible equipment will be used to monitor the participants inside the MRI scanner. Study participants will wear ear plugs and/or ear protection to avoid noise disturbances from the MRI scans, and will be equipped with an alarm call button in case of emergency.

A consultant radiologist will review all MRI scans. In the rare case of pathological findings, the radiology department at Bispebjerg and Frederiksberg Hospital has instructions for further treatment procedures. Briefly, the participant will be informed of the possible pathological findings and the participant will be scheduled for further radiological testing and referred to a specialist in neurology. Prior to inclusion in the study, participants will be informed of this procedure. If the participants do not wish to be informed of potential pathological findings, we reserve the right to exclude them before commencement of the MRI scan.

Likewise, the experimental pain testing conducted in the parallel study (Clinicaltrials.gov identifier: NCT02527395) do not cause damage to the skin or have any other long-term adverse effects. In rare cases, changes comparable with a first degree sunburn may appear. This study will be conducted in accordance with the principles of the Declaration of Helsinki. The protocol is approved by the local Danish Research Ethics Committees (identifier: H-15010473), and the Danish Data Protection Agency (identifier: RH-2015-149). This study is also reported on the international database (clinicaltrials.gov identifier: NCT02567318).

Informed written consent will be received from all volunteers before inclusion in the trial. Relevant provisions of the Research Ethics Committee regarding informed consent will be followed. Negative, positive, conclusive, and inconclusive test results will be published. We aim to publish the results in two separate publications, the first of which will report the primary and secondary outcomes, and the exploratory outcomes 1-4, and the second publication will report the exploratory outcomes 5 and 6.

## Abbreviations

3D: three-dimensional
ANOVA: analysis of variance
BTS: brief thermal sensitization
DTI: diffusion tensor imaging
EBLUPS: estimated best linear unbiased predictors
HADS: Hospital Anxiety and Depression Scale
HPDT: heat pain detection threshold
ICA: independent component analysis
MNI: Montreal Neurological Institute
MRI: magnetic resonance imaging
PCS: Pain Catastrophizing Scale
p-TS: pain during 1 minute of thermal stimulation
rs-fMRI: resting-state functional magnetic resonance imaging
TBSS: tract based spatial statistics
VAS-AUC: visual analog scale-area under the curve
